## Methods

### Design

This paper describes a pilot RCT to assess the feasibility of a phase 3 RCT examining the effects of an individualized, partly supervised, home-based exercise intervention in LTx and OLT recipients. The study is being conducted at the Toronto General Hospital in Toronto, Canada, and ethical approval was obtained from the research ethics board at the University Health Network (study ID: 20-5185). The study was registered at ClinicalTrials.gov NCT04965142. Informed written consent will be obtained from all participants before starting any research activities.

This protocol follows the SPIRIT (Standard Protocol Items: Recommendations for Interventional Trials) guidelines [38], the CONSORT (Consolidated Standards of Reporting Trials) statement [39], and the Consensus on Exercise Reporting Template [40]. Two patient partners are part of the research team, have provided input into the study design, and will contribute support and their lived experience throughout the study. The research team will hold meetings with patient partners every 3 to 6 months to collect feedback on study progress, assess concerns, and work on knowledge translation tools once the study is completed. Modifications to the study protocol will be approved by the research ethics board before implementation, communicated to funding agencies, and outlined in future publications.

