### Study Assessments

#### Overview

Study assessments will be conducted at baseline and 2, 6, and 12 weeks. For a detailed list of assessment procedures by time point, refer to Tables 1 and 2. For participants unable to come on-site, assessments will be performed remotely from participants’ homes, and blood screenings and electrocardiogram assessments will be conducted at local laboratories. During remote assessments, participants will be supervised by the research team using videoconferencing. To ensure the safety and confidentiality of participants undergoing remote assessments, the research team will ascertain the participant’s identity, home address, and phone number. An assessment of the suitability of the participant to perform physical assessments will also be performed before starting any interaction with participants (eg, self-reported breathlessness, dizziness, and chest pain). Participants will be instructed to discontinue exercise testing if they experience any symptoms or feel unwell.

**Table 1 table1:** Assessment of primary study outcomes by time point.

Primary outcomes	Assessment measures	Time point
Recruitment	Consented patients over total of eligible patients approached	During study period
Retention	Measured by attrition throughout the intervention period	During study period
Adherence	Completion of at least 70% of intervention elements	During study period
Satisfaction	Satisfaction survey	Weeks 2, 6, and 12^a^

^a^For usual care, satisfaction will be evaluated at baseline and 12 weeks.

**Table 2 table2:** Assessment of secondary study outcomes by time point.

Secondary outcomes	Assessment measures	Time point

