#### Intervention Group

##### Overview

Our exercise program was informed by expert guidelines on exercise prescription in solid organ transplant recipients [12,20,41] and will be delivered by an exercise professional with experience in chronic disease management. Following the baseline assessment and randomization, intervention participants will receive an individualized, home-based exercise program consisting of aerobic and resistance training exercises for 12 weeks. The exercise prescription targets the Canadian Physical Activity guidelines [42], which recommends ≥150 minutes of at least moderate-intensity aerobic training per week and at least two days per week of resistance training for major muscle groups. Daily exercise practice will be unsupervised; however, the exercise professional will provide the exercise prescription during the first training session via videoconference, including the following: an assessment of the participant’s ability to exercise independently in their home environment (eg, review of the participants’ heart rate, blood pressure, and history of any pertinent injuries), demonstration and review of training techniques, and proper use of their Fitbit and exercise equipment.

Participants will also receive a detailed manual describing the importance of exercise and self-management skills for exercise behaviors based on the theory of planned behavior and social cognitive theory adapted from previous studies [43,44]. The manual will highlight the basics of exercise training, the importance of routines, principles related to exercise progression, and photographs with descriptions of the prescribed exercises. After the initial training session, the exercise professional will follow up weekly (via videoconference) with study participants to address potential barriers to exercise, provide motivational support, review symptoms or adverse events during independent training at home, and prescribe training progression. The exercise program will be tailored to the specific and changing needs of the participant, taking into consideration comorbidities, exercise capacity, physical function, and availability of training equipment. Details on exercise prescription for the intervention group are briefly provided and described in Table 3.

**Table 3 table3:** Exercise prescription details for participants in the intervention group.

Modality and frequency	Intensity	Time and volume of exercise	Type of exercise	Progression

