##### Safety Precautions for Remote Exercise Training

Participants will be instructed to discontinue exercise training if they experience any symptoms or feel unwell and will be strongly encouraged to immediately contact a member of the research team upon noticing any adverse events. Participants will be advised to reduce the intensity of their training if they reach ≥15 on the Borg RPE scale, if oxygen saturation is less than 85%, or if they experience any symptoms (eg, severe shortness of breath). If participants report chest pain or discomfort (ie, uncomfortable feeling of pressure, pain, squeezing, or heaviness in the chest spreading to the shoulder, arms, neck, and back), they will be instructed to stop and rest and seek emergency assistance if the discomfort persists for 5 minutes.

Participants who communicate medically concerning adverse events (eg, cardiovascular event or disease exacerbation) or contraindications to the exercise program will have their training suspended until clearance is provided by the study physician and the exercise professional. If participants sustain an injury because of participating in the study, the study team will ensure that appropriate medical treatment is received.

Before initiating any interaction with study participants, the study team will perform an objective assessment (ie, by measuring oxygen saturation, blood pressure, and heart rate if participants have a pulse oximeter or a blood pressure monitor at home). A subjective assessment of the study participants (eg, self-reported breathlessness, dizziness, and chest pain) will ascertain their suitability to proceed with testing, training, and progress with the exercise prescription. The study team will discuss with participants aspects of their home environment, availability and suitability of exercise training equipment, home walking space, and any potential safety concerns (eg, footwear, rugs, clutter, and pets). During the internet-based training sessions, participants will be supervised by the study team via a videoconference platform. Participants will be able to book additional sessions with the exercise professional if any concerns or questions arise.

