### Statistical Procedures

#### Sample Size

The sample size of 40 (10 per study group and transplant type) is in keeping with the recommendations for a pilot study to assess feasibility [54]. A power calculation was not performed for the secondary outcomes, as the main purpose of this study is to determine feasibility and obtain point estimates for a larger RCT. The liver transplant and LTx program at the University Health Network each has approximately 150 to 200 recipients per year. Furthermore, the rates of PTMS among LTx and OLT recipients range from 30% to 50%; thus, we anticipate an approximate eligible pool of 50 transplant recipients per year for each organ group. Our previous consent rates for rehabilitation studies in these populations have been approximately 30% to 50% [55,56].

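### The home-training safety rules give two different actions, stop and reduce intensity, for the same trigger of any symptoms

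*Protocol article*

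**What the plan says.** All of this is in the protocol article.

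- **Safety Precautions for Remote Exercise Training, first sentence:** "Participants will be instructed to discontinue exercise training if they experience any symptoms or feel unwell". The sentence also strongly encourages participants to contact the research team at once about adverse events.
- **Same section, next sentence:** participants are advised to lower the training intensity at a Borg rating of 15 or more, at saturation below 85%, "or if they experience any symptoms (eg, severe shortness of breath").
- **Same section, further rules:** chest pain or discomfort has its own rule: stop and rest, then seek emergency help if it lasts 5 minutes. Medically concerning adverse events that a participant communicates suspend training until it is cleared. At staff contacts, a subjective check covering "self-reported breathlessness, dizziness, and chest pain) will ascertain their suitability to proceed with testing, training" and progression is made.
- **Study Assessments, Overview (remote testing):** "Participants will be instructed to discontinue exercise testing if they experience any symptoms or feel unwell".
- **Intervention Group, Overview:** "Daily exercise practice will be unsupervised". The exercise professional follows up weekly by videoconference, in part to "review symptoms or adverse events during independent training at home".

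**The concern.** A stopping rule is useful only if it names one action for each trigger. Here, two consecutive sentences name two actions for any symptoms, and the text does not say which prevails.

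The rule is applied mostly where no member of staff is present. Between weekly contacts, a participant who becomes severely breathless or dizzy in mid-session has to decide alone. One sentence tells that person to stop; the other lets the session go on at a lower level. What is at stake is the safety of transplant recipients exercising at home. Safety is also among the feasibility outcomes of this pilot, so the rule is likely to be carried into the larger trial it prepares.

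**Working it through.** No calculation tests this point. The check compares the two sentences and then looks for anything in the article that reconciles them.

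**Side by side**

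| | First sentence | Second sentence |
|---|---|---|
| Addressed to | Participants | Participants |
| Activity | Exercise training | Exercise training |
| Trigger | Any symptoms, or feeling unwell | Any symptoms (example: severe shortness of breath), Borg 15 or more, or saturation below 85% |
| Action | Discontinue | Reduce intensity |

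The symptom trigger is worded identically in both. Only the action differs.

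**Readings that might remove the conflict**

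1. *Mild symptoms mean reduce, severe symptoms mean stop.* The text rules this out. The only example under the weaker action is a severe symptom, and the first sentence covers every symptom.
2. *One sentence is about testing and the other about training.* Both are about training. Testing is covered separately under Study Assessments, which uses only the stop rule.
3. *Stop now, then resume later at lower intensity.* No such sequence is stated. The second sentence sets the same action for a Borg rating of 15 or more, which is a reading taken within a session.
4. *Another rule takes over.* The stop-and-rest rule is limited to chest pain or discomfort. Suspension follows an event the participant has already communicated. The suitability check is made at contacts with staff, and symptom review is weekly. None of these says what to do when breathlessness or dizziness starts during an unsupervised session.

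**Which sentence is out of line**

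The testing rule uses the stop action for the same trigger. The suitability check treats breathlessness and dizziness as possible reasons not to proceed with training. Both agree with the first sentence, so the second is the outlier.

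**Who is covered**

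The Sample Size section gives "The sample size of 40 (10 per study group and transplant type"). The intervention arm is therefore 10 lung + 10 liver = 20 of the 40 participants, and the rule applies to all 20. The article reports no symptom rate, so no count of affected sessions can be derived.

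**The case against.** The best case for the text as it stands has four parts.

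- **Force of the verbs.** The stop rule is an instruction and the reduce rule is advice, so the instruction could be taken to prevail; a participant who stops has not breached the advice. The second sentence also lists markers of exertion, so its symptoms could mean over-exertion during a bout. The article states neither distinction, and the severe example fits the second poorly. A participant still receives two directions.
- **What participants actually receive.** They get a first videoconference training session and a detailed manual, and the article says standard operating procedures exist for all protocol elements. None of these is shown, and they may well be consistent. This stands as a limit: the finding concerns the protocol text, and a harmful instruction to a participant is a possibility, not a documented fact.
- **Other safeguards.** Besides the rules listed above, participants can book extra sessions, and active cardiovascular disease is an exclusion, with chest pain, dizziness or fainting in the last 3 months given among its examples. These reduce the exposure. They do not govern a new symptom in mid-session.
- **A graded rule may be better.** Training runs at 65% to 85% of estimated maximal heart rate, where some breathlessness is plausible, and stopping for every symptom could be too blunt. The testing rule and the suitability check do not by themselves settle this clinical choice. That is fair, and the remedy leaves room for a reduce-only tier. It does not defend the present wording, which puts a severe symptom in the weaker tier.

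**Conclusion.** The point holds. The section attaches two incompatible actions to one trigger in consecutive sentences, and nothing in the article resolves the conflict. It concerns symptoms other than chest pain, such as severe breathlessness or dizziness, that begin during unsupervised home sessions. It applies to all 20 planned intervention participants.

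Confidence in the textual contradiction is high, because it rests on the article's wording alone. How often the conflict would matter is unknown, since there is no symptom rate and the manual is not shown.

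This is a patient-safety wording error that should be fixed. It leaves the sample size unchanged, and no effect on the adherence criterion, the safety outcomes or the analysis is claimed.

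**What to change.** In the reduce-intensity sentence, delete the clause on symptoms and its example. Keep the reduce action for a Borg rating of 15 or more; the saturation trigger stays as it is, and no claim is made about it here. Symptoms or feeling unwell then lead to stopping and contacting the research team, in line with the first sentence and with the testing rule.

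If the study physician wants a reduce-only tier, it should list named mild symptoms, and severe breathlessness should not be among them.

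Use the same wording in the participant manual and the daily log.

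The cost is one deleted clause, matching text in two participant documents, and the approval step in the Design section: "Modifications to the study protocol will be approved by the research ethics board before implementation". No extra visits, staff or patients are needed.

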#### Control Group

The control group will meet with the exercise professional at the start of the study to highlight the benefits of physical activity and will be provided with physical activity monitors (Fitbits) to track their daily physical activity levels (minutes and steps) along with physical activity logs to record daily physical activity. The study team will correspond with the control group every 2 to 4 weeks during the study period to see if any questions arise regarding the physical activity logs and trackers. After 12 weeks, the control group will have the option of receiving an exercise session with the exercise professional. During this session, study participants will receive general physical activity and exercise training recommendations and an exercise manual tailored to the needs of LTx and OLT recipients.

### Outcomes

A schedule of study outcome measurements is provided in Tables 1 and 2.

#### Primary Outcomes

##### Feasibility

The feasibility of a larger RCT to assess intervention efficacy (ie, phase 3 clinical trial) will be assessed through recruitment rates, program adherence, contamination, attrition, and safety at the end of the 12 weeks.

##### Recruitment

The recruitment rate will be defined as the proportion of randomized patients relative to all eligible patients approached for study participation. A consent rate of 30% or greater has been established as our criteria to determine study feasibility for future projects. The reasons for study nonparticipation will be collected.

##### Retention

Retention for the whole study and per group will be determined by the number of participants completing the final study assessment compared with the number of randomized participants. A retention rate of 80% or greater has been established as our criteria to determine study feasibility for future projects. The reasons for dropping out or interruptions to training will be collected.

##### Adherence

Adherence to the prescribed exercise program will be defined as completion of at least 70% of intervention components by the intervention group. This will be ascertained during weekly communication with participants and through a review of completed daily exercise logs, indicating exercise days, duration, intensity, and frequency of exercise sessions. Similarly, contamination in the control group will be assessed using physical activity logs.

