There is limited literature surrounding the experiences of transplant recipients concerning knowledge of, motivation for, and barriers to exercise training, which limits our understanding of the feasibility of real-world implementation. Several strategies to engage participants in exercise interventions and optimize adherence have been explored for chronic diseases [9]. The literature on chronic disease management highlights that adherence can be increased by providing close support by an exercise professional, simplifying the number of exercises, and fostering self-efficacy for exercise [33]. The support and coaching by the exercise professional can be enhanced with the use of telecommunication and the ability of the participants to readily contact the health coach as needed [26,27]. In addition, focusing on four sources of self-efficacy built into an exercise program (mastery, vicarious experiences, verbal feedback, physiological and emotional state) has been shown to significantly improve exercise adherence in patients with cardiometabolic risk factors [34,35] but has not been applied to transplant recipients.

These gaps in knowledge are important to address as optimal effects on PTMS are likely achieved if exercise is performed with sufficient volume (at least moderate intensity, accumulating ≥150 min/week) [36]. However, it remains unclear whether this training dose is optimal or if it can be achieved with a home-based program targeting metabolic risk factors starting at 12-18 months after transplantation, a critical period prognostic of long-term PTMS and cardiovascular morbidity [37]. Before these efficacy questions can be addressed with an appropriately powered RCT, a pilot study evaluating the feasibility of a home-based exercise program is needed.

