### Aims

The specific aims of this study are (1) to evaluate the feasibility of a 12-week individualized, home-based aerobic and resistance training program in LTx and OLT recipients at 12-18 months after transplantation and (2) to assess estimates of intervention efficacy on PTMS risk factors, exercise self-efficacy, and HRQL. We hypothesize that we will achieve a recruitment rate of 30% of eligible LTx and OLT recipients, participants in the intervention group will demonstrate an adherence rate of ≥70% to the prescribed exercise dose (including attainment of the prescribed exercise progression over time) and that PTMS risk factors, self-efficacy, and HRQL will be improved in the intervention group compared with the control group.

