## Discussion

### Overview

PTMS is a common sequela of solid organ transplantation and is associated with increased cardiovascular morbidity and mortality among LTx and OLT recipients [57,58]. Studies in the early posttransplant period (<1 year) have shown the benefits of facility-based exercise training on physical function and HRQL, but to date, only a recent study has evaluated the effects of 3 months of telehealth sessions on metabolic risk factors in OLT recipients [32]. These teleconferencing group sessions comprised alternating exercise and nutrition-based interventions with a few personalized sessions, which demonstrated improvement in PTMS, diet adherence, and mental HRQL. However, it remains unclear whether home-based exercise programs can be delivered with a sufficient exercise dose and adequate adherence to have effects on metabolic risk factors and exercise self-efficacy in both LTx and OLT recipients. This is an important consideration given the significant differences in routine perioperative rehabilitation practices across solid organ transplant recipients. For instance, LTx recipients participate in both pre- and posttransplant rehabilitation [41], whereas many centers do not have a dedicated exercise program for OLT recipients and may impact self-efficacy, adherence, and perception related to exercise training [12,59]. Thus, this protocol outlines the methodology of a pilot study implementing a partly supervised personalized home-based exercise program for LTx and OLT recipients as the first key step in developing future clinical trials to offset the high morbidity associated with PTMS.

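### The pilot asks whether a home programme can deliver at least 150 min/week, but its only related criterion is 70% completion of an individualized prescription, so it could be called feasible without answering that

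*Protocol article*

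**What the plan says.** **The question.** The Background section of the Protocol article describes the volume likely to be needed for a metabolic effect as "at least moderate intensity, accumulating ≥150 min/week" and then says "it remains unclear whether this training dose is optimal or if it can be achieved with a home-based program". The Abstract raises the same doubt. The Discussion (Overview) names two unknowns together: "whether home-based exercise programs can be delivered with a sufficient exercise dose and adequate adherence".

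**The criterion.** Under Primary Outcomes, Adherence: "Adherence to the prescribed exercise program will be defined as completion of at least 70% of intervention components by the intervention group". Table 1 has "Completion of at least 70% of intervention elements". The Aims section hypothesizes an "adherence rate of ≥70% to the prescribed exercise dose (including attainment of the prescribed exercise progression over time"; this too is relative to what each person was prescribed. The other numerical criteria are recruitment of 30% or more and retention of 80% or more.

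**The prescription.** The Intervention Group overview says it targets guidelines of at least 150 min/week of aerobic training plus at least two resistance days, and also that "The exercise program will be tailored to the specific and changing needs of the participant". Aerobic Training gives three to five 30-minute sessions per week. Table 3 lists 30 minutes on 3 to 5 days beside a weekly volume of at least 150 minutes, with progression up to 60 minutes per session.

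**The data and analysis.** Daily logs record days, duration, intensity and frequency, and every participant gets a Fitbit. Proposed Data Analyses summarizes adherence, satisfaction, contamination, attrition and safety. Attained weekly minutes are not listed.

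**The concern.** Adherence and attained dose are different quantities. Adherence is a ratio whose denominator is each participant's own prescription; attained dose is an absolute amount. The document treats them as separate unknowns, but only the first became an outcome with a threshold.

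If recruitment, retention and adherence all meet their marks, the natural conclusion is that the programme is feasible and a phase 3 trial can follow. That conclusion would not show whether participants trained at the volume the authors link to metabolic benefit. It would also make a flat metabolic estimate hard to interpret. The limitations text already allows that 12 weeks may be too short, and without attained dose, too short could not be told apart from too little. The eligibility criteria use the same yardstick, since people already reporting 150 min/week or more of moderate aerobic activity are excluded as active.

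**Working it through.** **The plan's own count.** 10 per study group and transplant type × 2 groups × 2 transplant types = 40, as stated, so 20 are in the intervention group. No power calculation bears on this point.

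**Inputs.** Target dose 150 min/week (Background, Table 3). Adherence cut-off 0.70 (Adherence, Table 1, Aims). Sessions 3 to 5 per week at 30 minutes (Aerobic Training). Ceiling 60 minutes per session (Table 3).

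**Assumption.** The document does not define components. Below they are read as aerobic minutes; another reading would change the figures.

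**Step 1: cut-off on a prescription of exactly 150 min/week.** 0.70 × 150 = 105 min/week, which is 150 − 105 = 45 minutes below the target.

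**Step 2: prescribed minutes = sessions × minutes; minutes at the cut-off = 0.70 × prescribed.**

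| Sessions/week | Prescribed at 30 min | 70% of it | Prescribed at 60 min | 70% of it |
|---|---|---|---|---|
| 3 | 90 | 63 | 180 | 126 |
| 4 | 120 | 84 | 240 | 168 |
| 5 | 150 | 105 | 300 | 210 |

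At 30 minutes, no frequency gives 150 at the cut-off. At the 60-minute ceiling, four or five sessions do and three do not.

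**Step 3: prescription at which 70% equals the target.** 150 / 0.70 = 214.3 min/week.

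**Step 4: illustration with progression.** Suppose sessions lengthen linearly from 30 to 60 minutes over 12 weeks (an assumed path; the document gives none). The mean session is 45 minutes. Average weekly minutes at 70% are 0.70 × 3 × 45 = 94.5, 0.70 × 4 × 45 = 126 and 0.70 × 5 × 45 = 157.5. The 150-minute mark is reached in 0, 3 and 7 of the 12 weeks respectively.

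**Step 5: precision of an attained-dose outcome with 20 participants.** For assumed counts of 10, 14 and 16 reaching the target, the exact 95% intervals are 27% to 73%, 46% to 88% and 56% to 94%. These are wide, but informative enough for a pilot to report.

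**A side finding.** Three to five 30-minute sessions give 90 to 150 min/week. Table 3 sets those same sessions beside at least 150 min/week. The two agree only at the top frequency or after progression.

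**The case against.** The strongest reply is that reaching 150 min/week is not a stated aim or hypothesis. It appears in the Background and Discussion, and the Background goes on to say that a feasibility pilot must come before the efficacy questions, which arguably leaves part of the dose question to the later trial. This is fair as to status: no stated aim is contradicted and no figure is wrong. But whether the dose can be achieved at home is a feasibility matter, and the text gives it as a reason for this pilot.

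Second, the denominator is not free-floating. The prescription targets at least 150 min/week, sessions can progress to 60 minutes, and the hypothesis includes attaining the prescribed progression. This stands, and it limits the point to a possible shortfall. It does not supply the missing measurement: a target is not an attained dose, and the progression clause is itself relative to the prescription.

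Third, any cut-off below 100% allows less than the full dose. That is true and is no error in itself. The difficulty arises only if the cut-off has to answer the dose question.

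Fourth, the data are collected, and an article may leave derivations to a fuller document. The raw data are indeed there, which makes the remedy cheap. However, the article itself fixes the primary outcomes and the threshold, and the mismatch lies between those and its own stated question.

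A reader might also infer that prescriptions will be cut for comorbidity, so that adherence stays high as dose falls. The document does not show this. Aerobic Training says sessions may be adjusted or divided, and its one example splits 30 minutes into two sessions of 15, which keeps the total.

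**Conclusion.** The point holds in limited form. The document presents attainable dose as a reason for the pilot, yet no feasibility criterion or planned summary measures it. Following the plan as written can give a finding of feasible that leaves the dose question open.

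The size depends on reading components as aerobic minutes. On that reading the criterion is met at 105 min/week on a 150 min/week prescription, or at 63 to 105 min/week on the stated 30-minute sessions, and a participant at exactly 70% needs a prescription of about 214 min/week to reach 150.

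It would go too far to conclude that most participants will fall short or that the adherence threshold is wrong. Participants may complete more than 70%, prescriptions may rise above 214 min/week, and the undefined term may mean something else. This is a worthwhile, inexpensive improvement and not a flaw that invalidates the pilot.

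**What to change.** - Add attained dose as a feasibility outcome separate from adherence: the number and proportion, with a 95% CI, of intervention participants reaching the protocol's own target of at least 150 min/week at the stated intensity, over a window fixed in advance.
- Report weekly minutes in both arms, in absolute terms, from the logs and Fitbit data.
- State that any conclusion about sufficient dose rests on this outcome and not on the 70% criterion.
- Define the components counted in the 70%.
- Reconcile the sessions under Aerobic Training (90 to 150 min/week) with the weekly volume in Table 3. No view is taken here on which is right.

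The cost is revised outcome wording and slightly more analysis, with no new data collection. The drawback is that the headline feasibility result may look less favourable.
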